#### 11.4.1 Datasets to be analyzed, analysis populations

We will prepare two data sets for the analysis:

- The per-protocol (PP) analysis set: includes only participants who complete the treatment according to the protocol (from the end of titration until 16 weeks of study).
- Intention-to-treat (ITT) analysis set: includes all randomized participants as originally allocated after randomization. ITT data set will be used for safety and efficacy analyses.

Due to the small sample size, no subgroup analysis is planned.

#### 11.4.2 Primary Analysis

The study design allows repeated measures (before and after) of the primary outcome and exploratory outcomes. We will use repeated measures analysis of covariance (ANCOVA) for the primary outcome while adjusting for HbA1c, BMI, and baseline TIR. A point estimate 95% confidence interval and two-sided p-value will be reported for the interventions (tirzepatide+AID vs SoC+AID), and a 5% level will be used to declare statistical significance. Residual values will be examined for an approximate normal distribution.

#### 11.4.3 Secondary Analyses

The secondary outcomes will be assessed using a mixed-effect linear model for repeated measures (MMRM) from baseline through 8, 12, and 16 weeks of treatment, respectively, with HbA1c and BMI as fixed effects, and baseline TIR as a covariate. A point estimate 95% confidence interval and two-sided p-value will be reported for the intervention (tirzepatide+AID vs. SoC+AID), and a 5% level will be used to declare statistical significance. Residual values will be examined for an approximate normal distribution.

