| Vital signs (BP, HR, Temperature c )                             | X         | X                         |                  | X  |    | X  |                 |
| ECG                                                                         | X         |                           |                  | X  |    | X  |                 |
| Body composition (BIA)                                                      |           | X                         |                  |    |    | X  |                 |
| Hepatic elastography (FibroScan®)                                           |           | X                         |                  |    |    | X  |                 |
| Device downloads (CGM and pump data)                                        |           | X                         | X                | X  | X  | X  |                 |
| SNAQ app data downloads                                                     |           | X                         |                  | X  |    | X  |                 |
| Activity tracker downloads                                                  |           | X                         |                  | X  |    | X  |                 |
| Questionnaires (DTSQs-c)                                                    |           | X                         |                  |    |    | X  |                 |
| AE/SAE assessment including assessment for clinical significance and severe | X         | X                         | X                | X  | X  | X  | X               |

|                                                                             |                |                |   |                |   |                |  |
|-----------------------------------------------------------------------------|----------------|----------------|---|----------------|---|----------------|--|
| hypoglycemia and DKA                                                        |                |                |   |                |   |                |  |
| Laboratory                                                                  |                |                |   |                |   |                |  |
| HbA1c (central)                                                             | X              |                |   |                |   | X              |  |

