### 11.2 Determination of Sample Size

Assuming a 1:1 randomization ratio, we calculated that a sample size of 42 participants (21 in each arm) would provide 80% power with a type I error rate (two-sided) of 5% to reject the null hypothesis with the following assumption: a standard deviation (SD) at baseline for TIR of 15%, a pre-post difference of TIR in the control group of 0.2%, a pre-post difference of TIR in the treatment group of 10.5%, a correlation of 0.7, and an attrition rate of 20%. The assumptions were taken from retrospective studies in T1D using tirzepatide (34,35).

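### The secondary model adjusts for baseline TIR where the endpoint's own baseline is needed, cannot be run as written for HbA1c, and leaves open whether baseline is also a response

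*Protocol*

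**What the plan says.** Section 11.4.3 of the protocol gives one model for all secondary outcomes: a mixed model for repeated measures "from baseline through 8, 12, and 16 weeks of treatment", "with HbA1c and BMI as fixed effects, and baseline TIR as a covariate". Chapter 5 lists these outcomes: HbA1c, TIR 07-23 h, time in tight range (TTR), time >10, >13.9, <3.9 and <3.0 mmol/L, and total daily insulin (TDI). They are tested hierarchically, HbA1c first, and the target is the group difference at week 16.

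Section 11.4.2 introduces the primary analysis with "The study design allows repeated measures (before and after) of the primary outcome and exploratory outcomes" and then names a repeated-measures ANCOVA "while adjusting for HbA1c, BMI, and baseline TIR". Chapter 5 and section 11.1 place the primary comparison at week 16. Neither 11.4.2 nor 11.4.3 names a treatment-by-visit term or says which contrast is the reported estimate.

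The baselines exist. The run-in phase (section 9.3.1) collects data to compute baseline glycemic metrics, average daily insulin is recorded at screening, and Table 1 schedules CGM and pump downloads at V2. Table 1 schedules HbA1c at V1 and V4 only. The visit lists in sections 9.3.4 and 9.3.6 and in Annex 6.1 agree.

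**The concern.** Three points in the model text do not fit the endpoints.

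1. Baseline TIR is the prescribed baseline covariate for endpoints that it may predict poorly. The gain from baseline adjustment comes from the correlation between covariate and outcome. For insulin dose and time below range, the endpoint's own baseline is the natural covariate, and section 11.4.3 does not name it. Because testing is hierarchical, one underpowered step can block all later ones. In the synopsis order TDI stands fourth, ahead of four other endpoints.

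2. HbA1c, the first step, has one post-baseline value. A model over weeks 8, 12 and 16 has nothing to fit at two of the three visits.

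3. The wording can be read as placing baseline among the responses while also adjusting for it. If the single reported group effect were then a main effect averaged over all time points, it would include one at which treatment cannot have acted, and it would not estimate the week-16 difference.

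**Working it through.** **Inputs (section 11.2).** SD of TIR 15; changes of 0.2 (control) and 10.5 (tirzepatide), so a net effect of 10.5 − 0.2 = 10.3 points; correlation 0.7; two-sided 5%; 80% power; 20% attrition; 21 per arm. The synopsis names ANCOVA of the change in TIR as the basis.

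**Reproducing the plan's 42.** Residual SD = 15 × √(1 − 0.7²) = 15 × √0.51 = 10.71. Per arm, n = 2 × (1.960 + 0.842)² × 10.71² / 10.3² = 16.98, so 17. For attrition, 34 / 0.8 = 42.5, which agrees with 42 to rounding. A change-score analysis (SD 11.62) needs 20 per arm, 50 in total. An unadjusted comparison (SD 15) needs 34 per arm, 86 in total. So the planned size rests on ordinary ANCOVA adjusted for the outcome's own baseline.

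**Wrong-baseline covariate.** Let c be the correlation of baseline TIR with the endpoint's follow-up value. The protocol does not give it, so a range is shown. I also assume that the own-baseline correlation is 0.7, as for TIR, and that the endpoint would have the planned standardized effect (10.3/15). Relative to own-baseline adjustment, residual variance and required N rise by (1 − c²)/(1 − 0.7²). Power is at 17 evaluable per arm.

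| c | 1 − c² | ratio to 0.51 | power, normal | power, t |
|---|---|---|---|---|
| 0.7 (equal to own baseline) | 0.51 | 1.00 | 80% | 77% |
| 0.5 | 0.75 | 1.47 | 64% | 61% |
| 0.3 | 0.91 | 1.78 | 56% | 53% |
| 0 | 1.00 | 1.96 | 52% | 49% |

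The loss differs by endpoint. Time >10 equals 100 minus TIR minus time <3.9, and TIR 07-23 h and TTR overlap heavily with TIR, so baseline TIR is a close proxy and the loss is probably small. Time >13.9 is in between. TDI, time <3.9 and time <3.0 are the most exposed.

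**HbA1c.** Section 11.4.3 calls for weeks 8, 12 and 16. Table 1 gives V1 (screening) and V4 (week 16). One post-baseline value remains.

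**Baseline as both response and covariate.** Take an effect of 10.3 at every post-baseline visit (assumed). Averaging the responses over baseline and k post-baseline values gives a group main effect of 10.3 × k/(k + 1):
- k = 1: 10.3 × 1/2 = 5.15
- k = 3: 10.3 × 3/4 = 7.73

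A simulation (17 per arm, SD 15, correlation 0.7 between all visits [assumed], 4,000 runs) gave:

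| Reported quantity | k = 1: estimate (SE) | k = 3: estimate (SE) |
|---|---|---|
| Main effect averaged over baseline | 5.11 (1.84) | 7.73 (2.18) |
| Week-16 contrast from treatment-by-visit term | 10.23 (3.73) | 10.22 (3.72) |
| Change contrast | 10.24 (3.96) | 10.22 (3.99) |
| Post-baseline ANCOVA | 10.22 (3.68) | 10.24 (3.74) |

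With k = 1, estimate and SE both halve, so the test statistic is that of ordinary ANCOVA. With k = 3, it is that of an ANCOVA on the mean of the three post-baseline values. The harm would be to the reported effect and its interval; no power is lost.

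**The case against.** The strongest reply is that baseline as a response is an inference. In 11.4.2 the before-and-after phrase describes the design and defines no outcome vector. In 11.4.3 the phrase starting from baseline may mean change from baseline, or simply the period covered. The target is week 16 in chapter 5 and section 11.1, and the interaction term and reported contrast are commonly left to an SAP, which may exist. This stands. A reader might infer that the headline TIR estimate will be halved, but the protocol does not say that a main effect averaged over baseline will be reported, and a week-16 contrast is not diluted. On the other side, section 9.2.2 describes the CGM and AID secondary outcomes as repeated measurements starting at baseline, so the reading is not far-fetched.

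A reader might also infer an inflated type I error. With a random-intercept covariance a week-16 interaction test can over-reject, but the protocol names no covariance structure, so no error-rate claim is supported.

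Nor does the covariate problem reach every secondary endpoint. HbA1c is itself in the model (presumably its baseline, though the text does not say so), and several CGM metrics track TIR closely. The two harms are also largely alternatives: if baseline is a response, a change contrast uses each endpoint's own baseline and loses little (SE about 4.0 against 3.7).

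Finally, the power figures carry TIR planning values over to endpoints for which the protocol claims no power. They are illustrative. With one post-baseline value the HbA1c model reduces to ANCOVA if baseline is only a covariate, so that mismatch is one of wording and no bias is shown.

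**Conclusion.** The point holds in a limited form. As written, and unless baseline is a response, TDI, time <3.9, time <3.0 and to a lesser degree time >13.9 are analysed without their own collected baseline. Randomization keeps the comparison valid; the cost is precision. Under the assumed correlations (0.7 own baseline, 0.3 to 0.5 baseline TIR), residual variance is about 1.5 to 1.8 times larger, and power falls from about 77-80% to about 53-64% for an endpoint with the planned standardized effect. If baseline TIR correlates more strongly with an endpoint, the loss shrinks, and it vanishes at 0.7.

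That the stated weeks 8, 12 and 16 model does not fit HbA1c follows directly from Table 1 and needs no assumption.

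Dilution of 10.3 to about 5.2 or 7.7 is conditional on two choices that the protocol does not make explicit: baseline among the responses, and a main effect averaged over it as the reported result. Even then the test decision is essentially unchanged. It is a reason to tighten the wording, not evidence that the primary analysis is biased. The sample size of 42 is unaffected.

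**What to change.** Reword sections 11.4.2 and 11.4.3.

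- **Primary:** ANCOVA, or MMRM on post-baseline periods only, with baseline TIR as covariate only, alongside HbA1c and BMI. Report the week-16 treatment contrast. This matches the ANCOVA behind the sample size.
- **Secondary CGM and insulin endpoints:** responses at weeks 8, 12 and 16 only; covariates are the endpoint's own baseline, HbA1c and BMI; include a treatment-by-visit term and report the week-16 contrast.
- **HbA1c:** single-visit ANCOVA at week 16 on baseline HbA1c.

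The measurement weeks in section 9.2.2 (4, 8 and 16) should be reconciled with the 8, 12 and 16 of section 11.4.3 in the same edit.

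The cost is protocol and SAP wording. All the baselines are already collected, no visit or assay is added, and the sample size does not change. The change should be made before analysis: the trial is open-label, and choosing among the possible readings later could depend on the data.

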#### **11.4.4 Interim analyses**

As a clinical study for 16 weeks, no interim analysis is planned.

#### **11.4.5 Safety analysis**

The entire ITT population will be included for safety analysis (such as AE/SAE). A table will be populated with the frequency of system-wide adverse events between two groups. Differences in safety outcomes will be examined between ITT groups using Chi-Square tests for categorical outcomes (any AE/SAE, clinically significance hypoglycemia, severe hypoglycemia, DKA) and non-parametric tests for continuous variables with non-normal distribution such as time spent in hypoglycemia on CGM.

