### 4.4 Safety Objectives

The study aims to assess preliminary data about the safety of the investigational medical product (IMP) (tirzepatide [*Mounjaro*®]) 5mg and its tolerability in terms of incidence of gastrointestinal side effects, hypoglycemia episodes, severe persistent hyperglycemia with ketosis, or DKA, serious adverse events (SAE) with a possible or more significant relationship to the use of the IMP (including expected and unexpected adverse drug reactions), other serious adverse events not related to the use of the IMP, and medical events of special interest (MESI) (**See Section 5.3**).

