### Safety Outcomes

- Occurrence of clinically significant hypoglycemia and severe hypoglycemia events (see **Annex 10** for hypoglycemia classification).
- Incidence of initiation of rescue therapy for severe persistent hyperglycemia and diabetic ketoacidosis episodes.
- Incidence of gastrointestinal side effects.
- Dehydration or renal acute events.
- Adjudicated hepatic or pancreatic AEs.
- Incidence of allergic and hypersensitivity reactions.
- Mean change in heart rate from baseline to 16 weeks.
- Treatment-emergent adverse events (TEAEs).
- Early discontinuation of study drug due to AEs.

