## 9.2.5 Assessments in participants who prematurely stop the study.

### Individual participant-stopping criteria.

Study drug administration may be stopped for any of the following reasons:

- Three or more episodes (separated by at least 120 minutes) of clinically significant hypoglycemia (Level 2) within one day (defined as 00:00 – 23:59) of the study, after excluding other causes such as the omission of meals, unexpected increases in physical activity, or exercise (or any other contributing factor more likely than the IMP) (**See Annex 10**).
- One or more episodes of severe hypoglycemia (Level 3) (**See Annex 10**).
- One or more DKA events unrelated to the participant's AID system malfunction.
- Adjudicated hepatic or pancreatic AEs.
- Incidence of allergic and hypersensitivity reactions.
- If a participant misses three or more consecutive doses of tirzepatide due to intolerable GI symptoms (e.g., nausea, vomiting, or diarrhea) that could be reasonably attributed to the study drug, despite the mitigation plan (**See Annex 8**).
- If a participant is diagnosed with an active or untreated malignancy (other than basal or squamous cell skin cancer, in situ carcinomas of the cervix, in situ, or grade group 1 [that is, Gleason 6 or lower] prostate cancer) after randomization.
- Dehydration or renal acute events.
- Post randomization calcitonin value  $\geq 35$  ng/L and increased at least 50% over baseline.
- Supraventricular arrhythmias and cardiac conduction disorders.
- If a female participant becomes pregnant.
- Investigator decides that, in the interest of the patient, it is not medically acceptable to continue participation in the study.
- Participants with a normal BMI at baseline will be closely monitored during clinical visits. The medication will be reduced to 2.5 mg or discontinued if there is a weight gain that exceeds 5% of total body weight or if weight reduction is too rapid (defined as greater than 1% of total body weight per week) following clinical evaluation

**Table 1** describes the time points of assessment. For the definition of these AEs/SAEs and for follow-up and procedures for participants who prematurely stop the study, see **Subsection 10.1.2**.

Criteria for suspending or stopping the study.

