#### Reportable AEs for Hypoglycemia and Hyperglycemia/Diabetic Ketoacidosis.

**Hypoglycemia:** Hypoglycemia is common in people with T1D. Clinically significant hypoglycemia (Level 2), defined as a blood glucose concentration of <3.0 mmol/L (<54 mg/dL) for at least 15 consecutive minutes in the CGM, typically leading to neuroglycopenic symptoms, will be reported as an AE if other causes, such as meal omission, unexpected increases in physical activity, or exercise, miscalculations of boluses by the participant or any other contributing factors, have been excluded. A diary for hypoglycemia events will be provided to participants for recording BG levels measured before treatment administration if taken, associated symptoms, treatment administered, and information about contributing factors, if applicable, as described previously.

Only severe hypoglycemia (or hypoglycemia level 3), defined as "a hypoglycemia event requiring medical assistance of another person due to altered consciousness and requiring another person to actively administer carbohydrate, glucagon, or other resuscitative actions" is reportable as an SAE. This means that the participant was impaired cognitively to the point that he/she was unable to treat himself/herself, was unable to verbalize his/ her needs, was incoherent, disoriented, and/or combative, or experienced seizure or coma. These episodes may be associated with sufficient neuroglycopenia to induce seizure or coma. If plasma glucose measurements are unavailable during such an event, neurological recovery attributable to restoring plasma glucose to normal is considered sufficient evidence that a low plasma glucose concentration induced the event.

**Hyperglycemic events/Diabetic Ketoacidosis (DKA):** Hyperglycemic event is only reportable as an adverse event when one of the following four criteria is met:

- 1) The event involved DKA, as defined by the Diabetes Control and Complication Trial (DCCT) and described here:

Hyperglycemic events are classified as DKA if the following are present (meeting all 4 criteria):

- a) Symptoms such as polyuria, polydipsia, nausea, or vomiting
  - b) Serum ketones >1.5 mmol/L or large/moderate urine ketones
  - c) Either arterial pH <7.30 or venous pH <7.24 or serum bicarbonate <15
  - d) Treatment provided in a healthcare facility.
- 2) Evaluation of treatment was obtained at a healthcare provider facility for an acute event involving hyperglycemia or ketosis.

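### Section 11.4.5 compares Level 2 hypoglycaemia between arms only as a category by chi-square, which discards episode counts and CGM time; a count-based comparison is better unless events are rare

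*Protocol*

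**What the plan says.** Section 11.4.5 (Safety analysis) compares the arms in the ITT population "using Chi-Square tests for categorical outcomes (any AE/SAE, clinically significance hypoglycemia, severe hypoglycemia, DKA"). The same sentence plans "non-parametric tests for continuous variables with non-normal distribution such as time spent in hypoglycemia on CGM". It states no comparison of the number or rate of episodes.

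Elsewhere the protocol describes Level 2 hypoglycaemia as something that recurs:
- Section 4.4 sets out to assess the drug and "its tolerability in terms of incidence of gastrointestinal side effects, hypoglycemia episodes".
- Section 10.1.2 has Level 2 "defined as a blood glucose concentration of <3.0 mmol/L (<54 mg/dL) for at least 15 consecutive minutes in the CGM". Annex 10 gives the same threshold and duration.
- Section 9.2.5 has an individual stopping criterion of "Three or more episodes (separated by at least 120 minutes) of clinically significant hypoglycemia (Level 2) within one day".

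Two further passages bear on the reading. The safety outcome in Section 5 is "Occurrence of clinically significant hypoglycemia and severe hypoglycemia events", with a pointer to Annex 10. Section 10.1.2 says that a Level 2 event "will be reported as an AE if other causes, such as meal omission, unexpected increases in physical activity, or exercise", and certain other causes, have been excluded.

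**The concern.** Next to any AE/SAE, severe hypoglycaemia and DKA, a categorical Level 2 outcome most naturally means whether a participant had at least one event. That wording is not spelled out. The alternative, a chi-square on pooled episodes, would be invalid because episodes within one person are not independent.

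On the any/none reading, the comparison loses information as events become more frequent. Once most participants in both arms have had an episode, the two proportions converge near 100% even if one arm has twice as many episodes. The comparison also takes no account of differing CGM time, although Section 11.2 assumes 20% attrition and Section 11.5 rules out imputation.

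Section 3.7 names low glucose as a risk that tirzepatide may increase. A non-significant chi-square on this outcome could be read as reassurance when the test had little chance of showing a difference.

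**Working it through.** **The plan's own figure.** There is none for this outcome: neither a Level 2 rate nor a power statement. The 42 participants come from the primary TIR comparison. SD 15 × √(1 − 0.7²) = 10.71; difference 10.5 − 0.2 = 10.3; n per arm = 2 × [10.71 × (1.960 + 0.842) / 10.3]² ≈ 17. Allowing for 20% attrition, 17 × 1.2 = 20.4, rounded up to 21 per arm, so 42 reproduces. It carries no information about power for hypoglycaemia events.

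**Inputs.** From the protocol: 21 per arm, 16 weeks, chi-square on a category, two-sided 5%. Assumed: negative binomial episode counts, dispersion k = 1 (k = 2 as a sensitivity), control mean μ of 0.1 to 10 episodes per participant, and equal CGM time for everyone, so that counts and rates coincide.

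**Share with at least one episode.** P(any) = 1 − (1 + kμ)^(−1/k), which for k = 1 is μ/(1 + μ). With the rate doubled, μ becomes 2μ in the second arm. Example at μ = 10: 10/11 = 91% against 20/21 = 95%.

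**Power for a doubled rate, 21 per arm, k = 1.** The uncorrected chi-square compares any/none; the Wilcoxon test compares the counts.

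| Control mean | Any event, control vs doubled | Chi-square | Wilcoxon |
|---|---|---|---|
| 0.1 | 9% vs 17% | 11% | 11% |
| 0.25 | 20% vs 33% | 17% | 16% |
| 0.5 | 33% vs 50% | 19% | 23% |
| 1 | 50% vs 67% | 19% | 29% |
| 2 | 67% vs 80% | 17% | 37% |
| 5 | 83% vs 91% | 11% | 41% |
| 10 | 91% vs 95% | 5% | 44% |

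Chi-square power falls as the mean rises from 1 to 10, while Wilcoxon power rises. Under no difference the Wilcoxon test rejects in about 4 to 6% of runs, so its gain does not come from an inflated error rate.

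**Other scenarios.**
- Halved rate at mean 5: chi-square 15%, Wilcoxon 38%.
- Tripled rate at mean 5: chi-square 17%, Wilcoxon about 80%.
- Dispersion 2, doubled rate, means 1, 4 and 8: chi-square about 13, 8 and 9%; Wilcoxon about 19, 21 and 21%. The gain is smaller when participants differ more.
- 17 per arm, k = 1, doubled rate, means 1, 4 and 8: chi-square about 20, 9 and 4%; Wilcoxon about 27, 31 and 37%.
- Negative binomial likelihood-ratio test, 21 per arm, k = 1, doubled rate, means 1, 2, 4 and 8: 39, 49, 53 and 58%. Under no difference it rejects in about 5 to 7% of runs, so it is slightly liberal and part of its advantage over Wilcoxon may be size.

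**The case against.** **Other hypoglycaemia analyses exist.** A reader might infer that the trial's hypoglycaemia conclusion hangs on this chi-square. The documents do not support that. Section 11.4.5 itself plans a non-parametric test of CGM time in hypoglycaemia. Percent time below 3.9 and below 3.0 mmol/L are secondary endpoints at week 16 and exploratory outcomes at weeks 8, 12 and 16. These use the CGM data continuously and do not saturate. What remains is narrower: duration is not episode frequency, and the event outcome listed in Section 5 still has only the chi-square. Time below 3.0 mmol/L also stands seventh in the Section 5 hierarchy and eighth in the synopsis, so as a secondary endpoint it is confirmatory only if every earlier test succeeds.

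**The events may be rare.** Section 10.1.2 makes Level 2 an AE only after other causes are excluded, and Section 11.4.5 lists it among AEs. If the cause-filtered events are meant, the mean could be well under one per participant, where counts gain nothing. This stands as a limit on the size of the point. It does not remove it: the Section 5 outcome points to Annex 10, which has no cause filter, and with rare events the Wilcoxon test loses almost nothing against chi-square.

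**Low power is mainly the sample size.** A reader might infer that counting episodes would make the comparison adequately powered. It would not: no count analysis run here reached 80% for a twofold change, and Section 4.4 calls the safety data preliminary. A rate ratio with its interval would at least show that uncertainty.

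**Occurrence can mean any event.** That is a fair reading of Section 5, and a reason to keep the proportion as a description. The 120-minute separation also belongs to a stopping rule, not to the event definition, so using it to count episodes is a choice that has to be declared.

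**Conclusion.** The point holds in limited form. For Level 2 hypoglycaemia, Section 11.4.5 fixes a test that ignores episode counts and observed CGM time, although the protocol defines a repeatable CGM event. If participants average about one or more episodes over 16 weeks (assumed means 1 to 10, dispersion 1, 21 per arm), chi-square power for a doubled rate is about 5 to 19%, against about 29 to 44% for Wilcoxon on counts. At means of 0.25 or less they are about equal, and with dispersion 2 the gain is smaller. All of this rests on assumed rates and dispersion and on reading the category as any/none, because the protocol gives no rate and does not spell out the categories. The effect is confined to one safety comparison; the primary outcome and the CGM time analyses are untouched.

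**What to change.** In Section 11.4.5:

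1. Take Level 2 hypoglycaemia out of the chi-square list, and keep the number of participants with at least one event as a descriptive row by arm.
2. Compare CGM-defined Level 2 episodes per participant per observed CGM time by a Wilcoxon test.
3. Report a rate ratio with 95% CI from an overdispersed count model, for example negative binomial with arm as factor and log CGM time as offset. Treat it as an estimate rather than as the test.
4. Define an episode for analysis by the 15-minute rule of Section 10.1.2 and Annex 10, and state that the 120-minute separation is borrowed from the stopping criterion in Section 9.2.5.
5. Report the cause-filtered Level 2 AEs of Section 10.1.2 separately.
6. Leave severe hypoglycaemia and DKA as participant counts.

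The cost is a few sentences and a little more programming on CGM data that the visit schedule already downloads from Visit 2 onwards. No participants, visits or procedures are added. The downside is small: the count model may be slightly liberal at this sample size, which is why the Wilcoxon test carries the comparison.
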